#### Secondary and exploratory outcomes

Secondary implementation and effectiveness outcomes, and exploratory effectiveness outcomes, are summarized in Tables 3 and 4. Secondary and exploratory outcomes will be examined using (1) PSH staff surveys, (2) Medicaid data analysis, and (3) PSH tenant surveys.

**Table 3 Tab3:** Secondary outcomes

Outcome	Measure	Data source	Timepoint(s)
*Secondary implementation outcomes*			
Adoption	Self-reported adoption of overdose prevention practices	Building self-assessment surveys^a^	Before first intervention wave, then as each of the 4 waves ends (5 timepoints)
Acceptability	Acceptability of intervention measure [49]	Staff surveys	5 timepoints as above
Appropriateness	Intervention appropriateness measure [49]	Staff surveys	5 timepoints as above
Feasibility	Feasibility of intervention measure [49]	Staff surveys	5 timepoints as above
Organizational priority	Adapted from Klein, et al. [50]	Staff surveys	5 timepoints as above
Sustainment	Fidelity checklist (see “Primary outcome” section)	Two blinded raters	8th month after end of each intervention wave^b^
*Secondary effectiveness outcomes*			
Staff knowledge about OD risk	Brief Opioid Overdose Knowledge (BOOK) Survey [51]	Staff surveys	5 timepoints as above
Staff stigma	Perceived Stigma Toward Substance Users Scale [52]	Staff surveys	5 timepoints as above
Tenant substance use emergency department (ED) visits	Visit diagnosis ICD-10 codes including poisoning, abuse, or dependence for alcohol or any drug (AHRQ HCUP classification list) [53]. Exploratory analyses will examine visits with specific diagnosis of poisoning (OD)	Medicaid data	5 timepoints as above plus 6th timepoint 6 months later
Tenant medication for opioid use disorder (MOUD) receipt	Tenant receipt of MOUD, MOUD initiation (new pharmacy claims) and adherence [54, 55]	Medicaid data	6 timepoints as above
Tenant specialty SUD treatment	Outpatient, inpatient, detoxification	Medicaid data	6 timepoints as above

*Legend*: Table shows secondary implementation and effectiveness outcomes for the stepped-wedge cluster RCT. Secondary implementation outcomes are measured via PSH staff surveys, except as otherwise noted. Secondary effectiveness outcomes are measured via PSH staff surveys and analysis of Medicaid claims data for PSH tenants

^a^Selected building leaders and key staff (e.g., staff champions) will complete self-assessment surveys as described in the “Primary outcome” section

^b^Buildings in the final intervention wave (wave 4) will complete self-assessment surveys at one additional timepoint, to allow completion of a final fidelity checklist to assess sustainment for this wave

**Table 4 Tab4:** Exploratory effectiveness outcomes from tenant surveys

Outcome	Measure
Overdose	Self-reported non-fatal overdose [56] and details about the overdose
Overdose risk behaviors	9-item instrument based on past research [57], with added item on using drugs behind a locked door
Naloxone use	Current possession, carrying, knowledge of sources, motivation to carry
Overdose risk knowledge	Brief Opioid Overdose Knowledge (BOOK) Survey [51]
Motivation for treatment/risk reduction	Motivation to initiate MOUD, obtain SUD treatment, and change overdose risk behaviors, with scales measuring importance, readiness, and confidence for making a change
Stigma	Perceived Stigma Toward Substance Users Scale [52]
SUD treatment and treatment barriers	Self-reported receipt of and barriers to SUD treatment, including MOUD [58]
PSH building services	Degree of comfort discussing substance use with building staff; self-report of building services related to substance use and overdose prevention

*Legend*: Table shows exploratory effectiveness outcomes for the stepped-wedge cluster RCT. Exploratory outcomes encompass tenant-level substance use and overdose-related measures. All are assessed via surveys administered to each tenant immediately before and 12 months following the start of their building’s intervention wave

*PSH staff surveys* will be conducted at five timepoints for staff from all participating buildings: once before the first intervention wave begins, and once as each of the four waves ends. All PSH staff with tenant-facing, supervisory, or leadership roles will be invited via e-mail to complete surveys. Invitation emails will include a hyperlink to a secure online REDCap survey. Invitations to participate in surveys will be non-coercive; it will be made clear that there will be no negative ramifications for their employment if staff decline to participate. A consent document will be included for staff to review prior to deciding whether to participate. Survey content is described in Table 3. Surveys are anticipated to take less than 20 min to complete.

*Medicaid data analysis* will use statewide Medicaid data to examine tenant-level effectiveness outcomes, as outlined in Table 3. Participating PSH buildings will provide investigators with PSH tenant identifying information. Investigators will use deterministic matching procedures to link this data with New York Medicaid data. After linkage, individual identifying information will be removed to create a de-identified Medicaid dataset for analysis; a building code will be retained and each tenant will be given a unique non-identifying study code to facilitate longitudinal analyses.

*PSH tenant surveys* will be used to examine exploratory effectiveness outcomes. These surveys will be administered twice for tenants of each participating building: immediately before that building’s intervention wave starts and approximately 12 months later. Paper surveys will be mailed to each tenant with a consent document, instructions for completion, and a self-addressed stamped return envelope. Tenants will also be offered the option to complete the survey by phone or online. Tenant surveys are anticipated to take approximately 30 min to complete. The study team will take multiple steps to increase survey participation rates, including explaining to tenants that the surveys are confidential and doing direct outreach in the PSH buildings. Survey content is described in Table 4.

Buildings participating in the study will complete agreements outlining provisions for data sharing (i.e., of staff and tenant contact information for survey distribution and tenant identifying information for linkage with Medicaid data) with the study team.

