#### Overdose prevention practices to be implemented

Buildings will receive support for implementing overdose prevention practices in three core categories: (1) overdose response; (2) harm reduction; and (3) support for substance use disorder (SUD) treatment. While the exact list of specific overdose prevention practices within each category is being refined in the study’s preparation phase, examples of anticipated practices are shown in Table 2.

**Table 2 Tab2:** Overdose prevention practices

Category	Overdose prevention practice examples
Overdose response	Create building-specific written overdose prevention and response plan; conduct formal debriefings after any overdose; provide support to staff and tenants related to trauma resulting from overdose; make naloxone readily available in the building; provide all tenants and staff with a naloxone kit and training on naloxone use and overdose response; systematically track information on overdoses in the building
Harm reduction	Uphold protocols that support a harm reduction model; take steps to minimize tenants using drugs alone without someone aware; train staff and tenants on harm reduction specific to the PSH environment and trends/risks related to the drug supply; have and document discussions with all tenants about safer drug use and overdose risk reduction; hold events and trainings for staff and tenants focused on reducing stigma toward people who use drugs; train staff in trauma-informed care; provide additional support for tenants during higher risk periods for overdose (e.g., transitions)
Support for SUD treatment	Educate staff and tenants about different SUD treatment types, including dispelling common myths about medication to treat opioid use disorder (MOUD); regularly assess tenant SUD treatment needs and interests; establish referral pathways to MOUD providers; provide access to peer support models; provide assistance to help tenants successfully engage in SUD treatment; provide support for tenants who are already in SUD treatment or are trying to reduce their drug use and/or who are maintaining sobriety

*Legend*: Draft planned categories and examples of specific overdose prevention practices. The complete list of overdose prevention practices will be refined and finalized during the preparation phase of the study. During the 6-month intervention period, PSH buildings will be supported in implementing these practices using the strategies described in Table 1

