## Abbreviations

CSH: Corporation for Supportive Housing
EPIS: Exploration, Preparation, Implementation, Sustainment framework
MOUD: Medication for opioid use disorder (e.g., methadone, buprenorphine)
NYC: New York City
PSH: Permanent supportive housing
RCT: Randomized controlled trial
SAB: Study advisory board
SRO: Single-room occupancy
SUD: Substance use disorder

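### MOUD initiation is measured by new pharmacy claims, a narrower rule than the protocol's own definition of MOUD, so any start dispensed and billed by a clinic would not count as an initiation

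*Protocol article*

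**What the plan says.** Table 3 (Secondary outcomes) has one row for tenant MOUD, with the measure given as "Tenant receipt of MOUD, MOUD initiation (new pharmacy claims) and adherence" and the source as Medicaid data. Of the three components, only initiation carries an operational rule, "MOUD initiation (new pharmacy claims"), and that rule names one claim type.

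The abbreviation list gives the scope of the term: "MOUD: Medication for opioid use disorder (e.g., methadone, buprenorphine"). Methadone is the first example named.

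Table 2 lists, among the practices that buildings will be helped to adopt, "establish referral pathways to MOUD providers". Neither that entry nor the surrounding text limits referral to providers whose medication is filled at a pharmacy.

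The paragraph on Medicaid analysis in the section on secondary and exploratory outcomes says that the study "will use statewide Medicaid data to examine tenant-level effectiveness outcomes, as outlined in Table 3". It does not describe the extract as limited to pharmacy files.

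Two neighbouring outcomes bear on the point. Specialty SUD treatment is a separate row of Table 3, measured as "Outpatient, inpatient, detoxification". The exploratory tenant survey (Table 4) records "Self-reported receipt of and barriers to SUD treatment, including MOUD".

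**The concern.** The component is named for MOUD in general but measured through one route of supply. Followed as written, a tenant who starts MOUD at a clinic, with the medication dispensed there and billed as a service, generates no new pharmacy claim and is not an initiator. Conversely, a tenant already on clinic-dispensed medication who moves to a pharmacy-filled product does generate a new pharmacy claim. Unless the look-back also searches clinic claims, that tenant could be counted as starting treatment when treatment is only continuing by another route.

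This matters here because referral is one of the ways in which the intervention is meant to act. If part of the response to referral goes through clinics, the initiation component would not register that part, and a null or weak result could be read as a failure of referral.

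**Working it through.** The plan gives no figure to reproduce. Its only power statement concerns the primary fidelity score. The check is textual, followed by an illustration over an assumed range.

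**Textual check**

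| Element | Scope in the article |
|---|---|
| MOUD (abbreviation list) | methadone and buprenorphine named as examples |
| Referral practice (Table 2) | MOUD providers, no route specified |
| Data source (Medicaid paragraph) | statewide Medicaid data, no file type specified |
| Receipt and adherence (Table 3) | no claim type specified |
| Initiation (Table 3) | new pharmacy claims |

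Initiation is the only element tied to one claim type. The mismatch has a practical effect only if some starts produce no pharmacy claim. The documents do not say how MOUD is dispensed or billed in New York Medicaid, so this is an assumption.

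**Illustration**

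Let m be the share of control-condition starts that are clinic-dispensed and billed as a service (assumed, range 0.1 to 0.7). Let RR_p and RR_c be the intervention's rate ratios for pharmacy and clinic starts.

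- Share of starts captured: 1 − m.
- Standard error of a log rate, with Poisson counts: proportional to 1/√(number of starts), so it grows by 1/√(1 − m).
- True rate ratio for all starts: (1 − m) × RR_p + m × RR_c.
- Rate ratio the rule observes: RR_p.

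| m | Captured | SE factor | True ratio if RR_p = RR_c = 1.5 (observed 1.50) | True ratio if RR_p = 1, RR_c = 2 (observed 1.00) | True ratio if RR_p = 2, RR_c = 1 (observed 2.00) |
|---|---|---|---|---|---|
| 0.1 | 90% | 1.05 | 1.50 | 1.10 | 1.90 |
| 0.3 | 70% | 1.20 | 1.50 | 1.30 | 1.70 |
| 0.5 | 50% | 1.41 | 1.50 | 1.50 | 1.50 |
| 0.7 | 30% | 1.83 | 1.50 | 1.70 | 1.30 |

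For example, at m = 0.3 with clinic starts doubled and pharmacy starts unchanged, the true ratio is 0.7 × 1 + 0.3 × 2 = 1.30, while the observed ratio is 1.00. The standard error factor is 1/√0.7 = 1.20.

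Three results follow.

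1. With equal relative effects on both routes, the rate ratio is unbiased. The loss is in precision and in the absolute difference: with control rate λ and common ratio RR, the true difference is λ(RR − 1) and the captured difference is (1 − m)λ(RR − 1), smaller by the share m.
2. With unequal effects, the observed ratio is wrong for MOUD as a whole. It is too low if referral acts mainly through clinics and too high if it acts mainly through pharmacies.
3. The table leaves out tenants who switch route. Their effect depends on the look-back rule and on how often switching occurs, and the article gives neither.

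The standard error factor describes count variation alone. Where between-building variation also contributes to the uncertainty of the estimate, the proportional increase would be smaller.

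**The case against.** The strongest objection is that the harm rests on a fact outside the documents: that some MOUD is billed as a clinic service and leaves no pharmacy claim. That stands as a limit on size. The shares used here are assumptions, and no single value can be defended from the article. The mismatch of scope does not depend on it, because the rule names pharmacy claims and the construct names methadone.

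A second objection is that this is a short gloss in a table cell of a condensed article. The row cites two measure sources, and they and the full protocol may define initiation more broadly. Code lists and look-back windows are ordinarily left to fuller documents, and their absence is not the complaint. The complaint is that the article does state a rule, and the natural reading of that rule is narrower than the thing measured. If a fuller definition exists, the published wording is incomplete and should be aligned with it.

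Three stronger readings are tempting, and the documents do not support them.

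- A reader might infer that the trial cannot see clinic-dispensed MOUD at all. The pharmacy wording attaches to initiation alone. Receipt and adherence carry no such limit, clinic care could appear under specialty SUD treatment, and the tenant survey asks about MOUD. None of these identifies a start from claims, so they do not repair initiation, but clinic MOUD is not shown to be invisible to the trial.
- A reader might infer that the estimated effect is necessarily diluted. The Statistical analysis section plans generalized linear mixed models, with a Poisson model as its example for visit rates. On a ratio scale, equal relative effects leave the estimate unbiased. Bias needs a differential effect, which is plausible but not established.
- A reader might infer that every tenant who switches route will be miscounted. That depends on a look-back rule that the article does not give.

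**Conclusion.** The point holds in a limited form. As written, the initiation rule covers a narrower set of starts than the MOUD that the protocol defines and that the intervention promotes. Assuming that between 10% and 70% of starts are clinic-billed, the component would miss that same share. Whether the rate ratio is also wrong depends on a further assumption, that the intervention moves the two routes differently; in the illustrative extreme where only clinic starts double, a true ratio of 1.10 to 1.70 would be observed as 1.00.

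The consequence is confined to one component of one secondary effectiveness outcome. The primary fidelity outcome and its power statement are unaffected. It is worth correcting before the Medicaid analysis, because the component is likely to be read as evidence on whether referral led to treatment.

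**What to change.** Define initiation as the first MOUD claim of any type, pharmacy or medical/clinic and including methadone, after a single MOUD-free look-back applied across both claim types. The common look-back prevents a change of route from counting as a start.

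If the sponsor prefers to keep the pharmacy rule, rename the component pharmacy-dispensed MOUD initiation and limit its conclusion to that route.

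The cost is a longer code list and slightly more programming. The source is already statewide Medicaid data, and the ED and specialty-treatment outcomes already draw on it for services rather than prescriptions, so no new data collection should be needed. Renaming costs only the wording, but it leaves clinic starts unmeasured as initiations.

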### Statistical analysis

To estimate effects of the intervention on the primary outcome, we will use a linear mixed model that incorporates both within- and between-cluster information and accounts for secular temporal trends. In particular, to assess the intervention effect, we will use a model with random site effects of the form: *Y*_it_ = μ + β_1_t + β_2_I_*it*_ + β_3_I_*it*_(*t* – s_*i*_) + b_*i*_ where *Y*_*it*_ is the fidelity checklist score in building *i* during period t, for t ∈ (0, 1, …, 4). Each period is 6 months; *t* = 0 is the first 6-month period. *I*_it_ is an indicator variable; I_*it*_ = 1 if building *i* has been assigned to implementation at period t and *I*_it_ = 0 otherwise. s is the period when implementation begins for building *i*. b_*i*_ is a random effect associated with each building *i* (the deviation of the intercept for the building from the overall intercept μ). Models will take into account a general time trend and allow for the intervention effects to grow over time following implementation. Models will be fit using the lme4 package using R software. Each hypothesis will be tested using a two-sided level of significance α = 0.05. Similar models will be used for analysis of the secondary implementation outcomes.

Implementation sustainment will be measured in the 8th month after the conclusion of each 6-month intervention wave. Paired-samples *t* tests will be used to compare each building’s fidelity scores at the end of its control period with scores during the sustainment period. For buildings assigned to early waves, there is also an opportunity to measure longer term (> 12 months) sustainment within the study measurement period.

Secondary effectiveness outcomes using Medicaid data and staff surveys will use generalized linear mixed models appropriate to each type of outcome (e.g., a Poisson model to compare visit rates). Health service use variables (e.g., ED visits) will be calculated as rates when appropriate (e.g., visits per study population per time period). For all secondary and exploratory analyses, we will examine the amount and type of missing data (e.g., missing at random or not at random) and implement appropriate statistical procedures for missing data as necessary. We will examine exploratory outcomes from tenant surveys using mixed-effects regression analysis. For the post-intervention survey time point we will conduct sub-analyses limited to tenants who have lived for at least 6 months in the building.

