Buildings participating in the study will receive education, training, and support for implementing the overdose prevention practices during their randomly assigned 6-month intervention (technical assistance) period. While buildings will be trained on and receive support in implementing each of the overdose prevention practices, we will not require and do not anticipate that all buildings will implement every practice. The primary goal of the study is to examine how successful buildings are in implementing the practices and we expect there to be heterogeneity across buildings.

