### Power and sample size

With 20 buildings participating in the study and 4 “steps” or waves in the stepped-wedge RCT (i.e., *n* = 100 observations over time across all buildings given 5 total time points per building), we will have at least 80% power to detect an increase of approximately two-thirds of a standard deviation (*d* = 0.69) or larger in the primary implementation outcome, a meaningful and feasible difference. This assumes a moderate correlation between scores for the same building at different time points (ICC = 0.5), reflecting stable differences among buildings. Even in the unlikely event that we do not retain 20 buildings in the study, with 16 buildings we would still have at least 80% power to detect an increase of about three-quarters of a standard deviation (*d* = 0.77) in the primary implementation outcome. To make these effect sizes more concrete, if the checklist score had a standard deviation of 8 and an average score of 15 under the control condition, the stepped-wedge design has 80% power to detect an increase of about 5 to 6 points on the checklist score (e.g., an increase from 15 to 20).

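### The primary model's only random term is a building intercept, so tests of the growth term β3 (and, mildly, the level effect β2) rest on a common effect and equal correlation at all lags that the protocol gives reason to doubt

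*Protocol article*

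**What the plan says.** The Statistical analysis section writes the primary model out in full, introducing it with the words "to assess the intervention effect, we will use a model with random site effects of the form". It contains a linear time trend, a common level effect β2 from the period in which support starts, a common growth term β3 per period since then, and a random term b_i, defined as the building's deviation from the overall intercept. No other random term and no robust variance is named. On testing it says: "Each hypothesis will be tested using a two-sided level of significance α = 0.05". Similar models are to serve the secondary implementation outcomes.

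The section on the practices to be implemented states that not every building will implement every practice. On how successful buildings will be, it says that "we expect there to be heterogeneity across buildings".

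The Primary outcome section describes a checklist scored partly from documents such as lease language, the building's overdose plan and training records. It is completed before the first wave and as each of four waves ends. With 6-month waves and 1-month buffers (Fig. 1 legend), neighbouring scores are about 7 months apart, and the first and last about 28.

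The Power and sample size section says: "we will have at least 80% power to detect an increase of approximately two-thirds of a standard deviation", with d = 0.69 for 20 buildings. On the correlation it adds: "This assumes a moderate correlation between scores for the same building at different time points", with an ICC of 0.5. It gives no variance for the intervention effect.

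**The concern.** A random intercept alone imposes two restrictions. Every building must gain the same amount from the support, and two scores from one building must be equally correlated whether 7 or 28 months apart. The first sits badly with the protocol's own expectation that buildings will differ in success. The second sits badly with the measure: a written plan or lease clause in place at one visit is likely to be there at the next, so neighbouring scores should be more alike than distant ones.

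If either restriction fails, the standard errors that the model reports can be too small. The term most exposed is β3, which carries the claim that effects grow after implementation. Slow drift within a building can look like growth, and with 20 buildings there is little to average it out. The power statement relies on the same restrictions and does not say that it assumes a common effect.

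**Working it through.** **1. The plan's own power figure.** Inputs from the protocol: N = 20 buildings, 5 per wave, T = 5 time points, ICC 0.5, two-sided α = 0.05. With total SD 1, τ² = σ² = 0.5. The Hussey-Hughes variance is

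Var(β2) = Nσ²(σ² + Tτ²) / [(NU − W)σ² + (U² + NTU − TW − NV)τ²].

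- The four waves have 4, 3, 2 and 1 exposed time points, so U = 5 × 10 = 50.
- W = 0² + 5² + 10² + 15² + 20² = 750.
- V = 5 × (16 + 9 + 4 + 1) = 150.
- Numerator: 20 × 0.5 × (0.5 + 2.5) = 30. Denominator: 250 × 0.5 + 750 × 0.5 = 500.
- Var = 0.06, SE = 0.2449, power at d = 0.69 = Φ(0.69/0.2449 − 1.96) = Φ(0.857) = 80.4%.
- For 16 buildings: Var = 24/320 = 0.075, SE = 0.2739, power at d = 0.77 = 80.3%.

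Both stated figures reproduce. With linear time and β3 in the model, power is 79.7% and 79.6%.

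**2. Growth term under autocorrelated scores.** The protocol gives no autocorrelation, so these values are assumptions. The planned model was fitted by REML to simulated 20 × 5 data (3,000 trials per scenario).

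| Correlation structure | True SD of β3 estimate | Mean model SE | Ratio | Rejection, z | Rejection, t on 18 df |
|---|---|---|---|---|---|
| Lag-1 correlation 0.7 | 0.172 | 0.127 | 0.74 | 15.2% | 12.6% |
| Lag-1 correlation 0.8 | 0.156 | 0.111 | 0.71 | 16.6% | 13.8% |
| 30% constant share plus AR 0.5 | – | – | about 0.8 | 12.8% | 9.8% |

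The third row has lag-1 correlation 0.3 + 0.7 × 0.5 = 0.65. As a hand check on the first row, 2Φ(−1.96 × 0.738) = 14.8%, close to the simulated 15.2%. Bias-corrected cluster-robust standard errors bring β3 rejection back to about 5% to 6%.

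**3. Level effect when effects vary between buildings.** The effect SD is also an assumption, in total-SD units. REML simulation (8,000 trials per scenario) with β3 in the model:

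| Effect SD | Reported / true SE of β2 | Rejection, z | Rejection, t on 18 df | Power of planned test at d = 0.69 |
|---|---|---|---|---|
| 0 | 0.98 | 5.6% | 4.1% | 79.5% |
| 0.22 | 0.97 | 6.2% | 4.8% | 78.5% |
| 0.32 | 0.96 | 6.1% | 4.5% | 77.3% |
| 0.50 | 0.94 | 7.2% | 5.4% | 74.2% |
| 0.71 | 0.92 | 8.0% | 6.0% | 69.2% |

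Repeat runs at 0.35, 0.5 and 0.7 gave power of about 77%, 75% and 70%. The shortfall in these large runs is about 4% to 8% from effect SD 0.32 upward; a smaller set of 2,000 trials per scenario reached 12%, with z rejection up to about 9%.

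**4. Power of a test that allows for the varying effect.** Analytic power at d = 0.69 is 75.6%, 71.4% and 64.3% at effect SD 0.345, 0.50 and 0.71, with detectable differences of 0.73, 0.77 and 0.83. The planned test's power in step 3 is higher because its own standard error is too small.

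**5. Whether the two problems share a cure.** A varying level effect hardly disturbs β3: rejection is 5.8% to 6.7% with z and 4.1% to 5.0% with t on 18 df. A varying growth rate does so moderately: slope SD 0.17 per period gives a ratio of 0.91 and 7.9% rejection with z. The large inflation in step 2 comes from autocorrelation, which a random intervention effect does not model.

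**The case against.** A reader might infer that the 80% power is wrong. It is not: it reproduces for 20 and for 16 buildings, and the correlation assumption is stated openly. What is missing is the statement that it also assumes a common effect.

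A reader might also infer that the standard errors are too small as a matter of fact. The protocol gives neither an effect variance nor an autocorrelation, so every figure in steps 2 to 5 is conditional. The expected heterogeneity may partly mean differences in attained level, which the intercept and ICC already cover. The top of the range is extreme: an effect SD of 0.7 around a mean of 0.69 implies that Φ(−0.69/0.7), about 16%, of buildings would lose fidelity because of the support. At an effect SD of 0.22, power is still about 78.5%.

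For β2, part of the excess rejection is only the z reference: it is 5.6% with no heterogeneity and stays near nominal with t on 18 df. The article names no reference distribution, and that detail may properly sit in an analysis plan not shown. Nor does autocorrelation at the assumed values undermine the power claim for β2, whose power stays at or above the stated level.

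All of this stands, and it limits the point for β2. It does not remove the point for β3, where a t reference still leaves 10% to 14% rejection. The article fixes the random structure itself.

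**Conclusion.** The point holds in a limited form and is a should-fix, a cheap improvement rather than a fatal flaw. The model's random structure is narrower than the protocol's own description of buildings and checklist supports.

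- **β3:** under assumed lag-1 correlations of about 0.65 to 0.8, standard errors are about 20% to 30% too small and rejection is about 12% to 17% (10% to 14% with t on 18 df). This is the larger problem.
- **β2:** under assumed effect SDs of 0.35 to 0.7, standard errors are about 4% to 12% too small, with rejection of about 6% to 9% with z and 4.5% to 6.4% with t on 18 df.
- **Power:** 80% is right for a common effect. For the planned test at d = 0.69 it is about 77%, 75% and 70% at effect SD 0.35, 0.5 and 0.7.

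The documents do not support saying that the power was miscalculated or that the test of β2 is seriously invalid.

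**What to change.** Keep the mixed model for estimation. Base tests and intervals for β2 and β3 on cluster-robust standard errors with a small-sample correction (CR2 or Kauermann-Carroll) and t on about 18 df, or on a permutation test over the wave allocation, which is simple here because randomization is unstratified. A permutation test addresses the hypothesis of no effect at all, so a separate statement about growth would still lean on the robust standard errors. A random intervention effect by building may be added, but is not sufficient alone because it leaves the autocorrelation untouched. Apply the same rule to the secondary implementation outcomes that use similar models.

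In the Power and sample size section, state that the 80% assumes a common effect, and show power over a range of effect SDs, for instance 0 to 0.7, for the test that will be used.

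The cost is analysis wording and a few lines of R, with no change to design or data collection. Intervals become slightly wider and the stated power less favourable. Moving from 1.96 to the t value of 2.101 alone gives Φ(2.817 − 2.101), about 76%, at d = 0.69 with a common effect.
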